## Abstract

**Background:**

Primary care is the principal clinical setting for the management of depression. However, significant shortcomings have been detected in its diagnosis and clinical management, as well as in patient outcomes. We developed the INDI collaborative care model to improve the management of depression in primary care. This intervention has been favorably evaluated in terms of clinical efficacy and cost-effectiveness in a clinical trial. Our aim is to bring this intervention from the scientific context into clinical practice.

**Methods:**

*Objective:* To test for the feasibility and impact of a strategy for implementing the INDI model for depression in primary care.

*Design:* A quasi-experiment conducted in primary care. Several areas will be established to implement the new program and other, comparable areas will serve as control group. The study constitutes the preliminary phase preceding generalization of the model in the Catalan public healthcare system.

*Participants:* The target population of the intervention are patients with major depression. The implementation strategy will also involve healthcare professionals, primary care centers, as well as management departments and the healthcare organization itself in the geographical areas where the study will be conducted: Camp de Tarragona and Vallès Occidental (Catalonia).

*Intervention:* The INDI model is a program for improving the management of depression involving clinical, instructional, and organizational interventions including the participation of nurses as care managers, the efficacy and efficiency of which has been proven in a clinical trial. We will design an active implementation strategy for this model based on the PARIHS (Promoting Action on Research Implementation in Health Services) framework.

*Measures:* Qualitative and quantitative measures will be used to evaluate variables related to the successful implementation of the model: acceptability, utility, penetration, sustainability, and clinical impact.

**Discussion:**

This project tests the transferability of a healthcare intervention supported by scientific research to clinical practice. If implementation is successful in this experimental phase, we will use the information and experience obtained to propose and plan the generalization of the INDI model for depression in the Catalan healthcare system. We expect the program to benefit patients, the healthcare system, and society.

**Trial registration:**

ClinicalTrials.gov identifier: NCT03285659; Registered 12th September, 2017.

## Background

Major depression is a highly prevalent disorder. The ESEMED study found the lifetime prevalence of major depressive disorder to be 10.6% in Spain, and 12-month prevalence to be 4% [1]. Depression is an undeniable public health problem, impacting not only patients and those around them but society as a whole [2]. In 2006, the cost of depression in Catalonia was 735 million euros. Direct healthcare costs represented only 21% of this total, while the majority were indirect costs related to the loss of labor productivity, inability to work, and premature death by suicide [3].

The most common mental health disorders, including depression, are managed in a primary care context [4]. A study conducted in primary care centers in Catalonia found that 14% of consecutive patients seen for any reason met criteria for major depression [5], and there is general consensus that the level of care at which depression can be managed most adequately and efficiently is primary care, in both developing and developed countries [6].

However, there are inadequacies in diagnosis, treatment, and follow-up for patients with this disorder [7], and clinical outcomes are frequently unsatisfactory [8]. In primary care, the monitoring of patients with depression is rarely planned, and there is inadequate supervision of clinical progress and adherence to treatment. Therefore, opportunities to take measures to increase adherence or adjust treatment when progress is not satisfactory are often missed [9].

In the management of depression there is a gap between what works and what actually happens in clinical practice and, because of this, clinical outcomes for depression do not correspond to what might be expected based on the efficacy of therapeutic interventions [10]. Studies have shown that collaborative care models are an appropriate strategy for closing this gap and achieving better health outcomes by bringing depression management closer to effective recommendations based on scientific evidence [11].

Collaborative care models are complex care programs based on the chronic care model and, in terms of structure, they encompass several components [12]. They are shared care models in which the roles of the various professionals involved in the management of depression are integrated into a common structure. The primary care physician is responsible for the clinical process of diagnosing and treating patients with depression. The care manager (often a nurse) assists the family physician in proactively following up on the patient’s clinical progress and adherence to treatment, and is the main person responsible for fostering patient empowerment and active participation in the therapeutic process. Psychiatrists assume different levels of involvement in different models, but in every model their role is to supervise and assist the primary care professionals in depression management, especially in cases with a less than satisfactory response or other complicating factors. Empowered and active patients, and by extension their family members, are generally considered to be part of the therapeutic team. A key aspect of collaborative care models is the systematic monitoring of the patient’s clinical progress and therapeutic response, which makes it possible to determine the most appropriate therapeutic approach for each patient’s clinical situation at any given time.

The efficacy of collaborative care models in the treatment of depression has been demonstrated in more than 70 clinical trials systematized in several meta-analyses [13]. Thota’s meta-analysis [14] evaluated 32 randomized clinical trials, and reported a standardized mean difference of 0.34, which, although conventionally interpreted as a small to moderate effect, is considered relevant in clinical and public health contexts given the prevalence and impact of depression. In general, it was concluded that there is sufficient scientific evidence to recommend the widespread implementation of these clinical models, which are especially applicable in the primary care setting [15].

Although the first models were developed and evaluated beginning 20 years ago almost exclusively in the United States [11], in recent years several clinical trials have demonstrated the efficacy, feasibility, and utility of these models in European public healthcare systems [16]. One of these studies is the INDI project, the basis for this project, which has developed and evaluated a collaborative care model adapted to the Catalan healthcare system [17].

Therefore, scientific evidence supports the clinical efficacy of collaborative care models for improving clinical results in depression, but although some useful cases have been reported [18], examples of the application or continued use of these interventions outside the research context are rare. A central challenge for healthcare systems is the implementation and generalization of health interventions that have been developed and evaluated in a research setting [19].

We aim to develop an effective strategy for implementing and generalizing the INDI model for depression management in the primary care context of the Catalan public healthcare system that is practical, effective, acceptable and perceived as useful by patients, healthcare professionals, and the organization. Our hypothesis is that the implementation of this method will give rise to the development of clinical processes that are better aligned with scientific evidence, which will result in clinical benefits for patients, and will prove economically sustainable and tenable over time.

## Methods/design

### Aim

The aim of this project is to develop a feasible strategy for the implementation of the INDI model under real healthcare conditions of primary care, initially in a limited geographical area but with the purpose of promoting the generalization of this model in the Catalan public healthcare system.

We will evaluate the success of the implementation based on its perceived acceptability and utility (to patients, professionals, and the organization) and on the integration and sustainability of the program into healthcare practice. The effectiveness of implementation will be assessed in terms of: (a) the quality and precision of the diagnosis of major depression; (b) suicide risk management; (c) the adaptation of the therapeutic management of depression to recommendations based on scientific evidence, including initial treatment selection, treatment duration, and joint management with psychiatry; (d) clinical results in depressed patients; and (e) financial costs associated with implementation.

### Design

This is a study of the implementation of a healthcare intervention with a quasi-experimental design and mixed measurement methods that include both qualitative techniques and analysis and quantitative indicators.

The design involves defining several geographic areas in which the INDI program will be implemented as well as other comparable areas which will serve as the control, where depression will be treated as usual.

### Settings and participants

This project will be completed in a limited area as a preliminary step to its eventual generalization.

Two public healthcare administrative organizations, the Gerència Territorial Camp de Tarragona (Catalan Health Institute) and the Servei d’Atenció Primària Vallès Occidental Est (Catalan Health Institute), will participate in this phase along with the primary care centers and mental healthcare providers in both regions (Fig. 1).

**Fig. 1 Fig1:**
[figure not shown]
Counties of Catalonia where the study will be carried out. Modified from Martí8888 [CC BY-SA 4.0]. Available at: https://commons.wikimedia.org/wiki/File:Catalonia_base_map_42_comarques.png

The Gerència Territorial Camp de Tarragona is the main primary care provider in the counties of Alt Camp, Conca de Barberà, Baix Camp, el Tarragonès and el Priorat in southeastern Catalonia and manages 20 primary care centers serving an assigned population of 323,740 people. The entity providing mental healthcare services is the Institut Pere Mata, with a community network including three adult mental healthcare centers located in the cities of Reus, Tarragona, and Valls.

The Servei d’Atenció Primària Vallès Occidental Est is the primary care provider for part of the county of Vallès Occidental, located in the Barcelona metropolitan area, and it manages 22 primary care teams serving an assigned population of 386,811 people. The Parc Taulí Corporation is the mental healthcare services provider and has two adult mental healthcare centers located in the city of Sabadell. This entity also manages a primary care center located in Sabadell that is participating in the project.

In each of these two regions, an area for testing the intervention and a comparable control area will be selected. The assignment of an experimental or control condition will not be random, but we will ensure that the areas are comparable in their sociodemographic, health, and organizational characteristics. Because the aim of the study is to test implementation under real conditions and we primarily anticipate using intention-to-treat analyses, exclusion criteria have not been established for centers or professionals as long as they are within the areas defined for this experiment.

All adult patients with a new diagnosis of major depression or a new episode of antidepressant treatment, defined as a new prescription (with no prior treatment for at least three months) associated with a prior diagnosis, will be considered for analysis. Patients with a psychotic disorder, bipolar disorder, a disorder associated with drug or alcohol use, dementia, mental retardation, postpartum depression, institutionalized patients and patients receiving treatment in at-home care programs will be excluded from the analysis because they are not part of the target population of the intervention. However, comorbidity of depression and other common mental disorders such as anxiety or sleep disorders do not constitute exclusion criteria.

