#### Quantitative evaluation

To measure the impact of the implementation of the model, we will evaluate a battery of quantitatively measurable indicators covering different aspects of quality, performance of the care process, and clinical outcomes: (a) diagnosis and initial evaluation (b) treatment, (c) clinical follow-up, (d) clinical outcomes, and (e) epidemiological indicators (Table 2).

**Table 2 Tab2:** Battery of indicators for the quantitative evaluation of the impact of INDI model implementation on clinical processes and outcomes

Area of evaluation	Indicator	Description
Diagnosis and evaluation	Diagnostic accuracy	The diagnosis of depression in the target population includes specifying the severity of the depressive episode (mild, moderate, severe, or currently in remission) as well as whether it is a single or recurrent episode.
	Diagnostic reliability	DSM-V criteria were used when making the diagnosis (MINI interview)
	Baseline evaluation of severity	In the baseline assessment the severity of symptoms was examined with a validated scale (PHQ9)
	Baseline evaluation of suicide risk	In the baseline assessment the risk of suicide was examined with a validated scale (MINI)
Treatment	Adequacy for mild depression	In mild major depression an antidepressant is not prescribed in the first eight weeks
	Adequacy for moderate or severe depression	In moderate or severe major depression treatment with antidepressants is initiated
	Adequacy for anxiolytic treatment in depression	The prescription of an anxiolytic as the only form of treatment for depression is avoided (i.e., without an antidepressant)
	Adherence to treatment, acute phase	12 weeks after initiating treatment the prescription has not been interrupted
	Adherence to treatment, continuation phase, relapse prevention	6 months after initiating treatment the prescription has not been interrupted
	Intensification of antidepressant treatment: switch	Proportion of new treatments in which the antidepressant is changed
	Intensification of antidepressant treatment: augmentation	Proportion of new treatments in which an antidepressant and an atypical antipsychotic or lithium are concomitantly prescribed
	Intensification of anti-depressant treatment: combination	Proportion of new treatments in which two antidepressants are prescribed simultaneously
Follow-up	Use of a validated scale	Number of times per patient in which a validated scale is used (PHQ9) in clinical follow-up

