### Analyses

The principal analyses will be by intention-to-treat, regardless of the degree of application and adherence to the INDI program guidelines by the patients, professionals, and healthcare centers or areas.

The quantitative analyses of this study will be based on the clinical records of all eligible depressed patients seen in the participating primary care centers. That is, we will work with the entire population and not with a sample, which provides the strengths to minimize selection bias and is based on an independent data collection [36].

At baseline, we will perform a comparative analysis between the areas assigned to the experimental group and the areas of the control group to ensure similarity between the characteristics of their health organizations and clinical practices related to depression.

Analyses of the quantitative variables will consist of both pre-post and intervention-control comparisons of the sets of indicators with quantitative results, with key control points at baseline and at 12 months.

Based on the nature and characteristics of the various questionnaires described in the measures section, the analyses will be carried out in a pre-post comparison framework or as a retrospective analysis at an advanced stage of the implementation process, which we have set at 12 months.

The interviews with focus groups will be recorded and transcribed in their entirety. We will then use a thematic framework analysis to classify and organize the data according to key topics, concepts, and predefined constructs that will be analyzed using qualitative techniques adapted from the normalization process theory [37] to identify barriers and facilitators in the various domains, focusing on ‘hot spots’, for example, dilemmas, conflict situations, and uncertainties.

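### Patients who enter the analysis by an antidepressant prescription have their result on the antidepressant-adequacy indicators largely preset, so these three indicators reflect the entry-route mix as well as care

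*Protocol article*

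**What the plan says.** Settings and participants gives two ways into the analysis: "a new diagnosis of major depression or a new episode of antidepressant treatment, defined as a new prescription". The prescription must follow at least three months without treatment and be tied to an earlier diagnosis, whose age is not limited.

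Analyses says the quantitative work is "based on the clinical records of all eligible depressed patients seen in the participating primary care centers" and consists of "both pre-post and intervention-control comparisons of the sets of indicators with quantitative results", with control points at baseline and 12 months.

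Table 2 has three adequacy indicators that turn on antidepressant prescribing:

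- Mild: "In mild major depression an antidepressant is not prescribed in the first eight weeks".
- Moderate or severe: "In moderate or severe major depression treatment with antidepressants is initiated".
- Anxiolytic: "The prescription of an anxiolytic as the only form of treatment for depression is avoided", where avoidance means that an antidepressant accompanies it.

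The first two are restricted by severity and the third not at all. None is restricted by entry route, and the start of the eight weeks is not given.

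**The concern.** The second entry route selects patients on the variable that these indicators score. It is also one-sided: someone with a prior diagnosis and a new episode enters by that route if an antidepressant is prescribed and does not if none is. The opposite decision is missing from the denominator.

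The Aim section lists the choice of initial treatment among the criteria for effective implementation, and the mild and moderate/severe indicators measure it most directly. If the share of prescription-only entrants differs between intervention and control areas, or between baseline and 12 months, these indicators can move although no prescribing decision changed. A real change can also be hidden. Equal shares are not assured: areas are not assigned at random, the INDI guideline tool supports diagnostic decisions, and Table 2 itself rewards recording whether an episode is single or recurrent.

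**Working it through.** The article gives no expected indicator rate, entry-route share or sample size, so there is no figure of its own to reproduce. The values of s and q below are assumptions.

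**Inputs**
- s: share of an indicator's denominator that entered only by prescription. A patient diagnosed and treated at the same time already qualifies by new diagnosis and is not counted in s.
- q: adequacy rate among new-diagnosis entrants.
- f: result preset for prescription-only entrants. f = 1 for moderate/severe and, at entry, for anxiolytic-only. f = 0 for mild if the eight weeks run from cohort entry.

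**Formula.** Indicator = (1 − s)·q + s·f. So moderate/severe = s + (1 − s)·q, and mild = (1 − s)·q. Each indicator has its own s and q.

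**Step 1: artefact with care unchanged.** Let s differ by 0.15 (0.40 against 0.25). The moderate/severe indicator moves by −0.15·(1 − q) and the mild indicator by +0.15·q.

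| q | Moderate/severe, s 0.40 → 0.25 | Change | Mild, s 0.40 → 0.25 | Change |
|---|---|---|---|---|
| 0.4 | 64.0% → 55.0% | −9 | 24.0% → 30.0% | +6 |
| 0.6 | 76.0% → 70.0% | −6 | 36.0% → 45.0% | +9 |
| 0.8 | 88.0% → 85.0% | −3 | 48.0% → 60.0% | +12 |

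The artefact is 3 to 12 points and runs in opposite directions on the two indicators. If s rose instead, the signs would reverse.

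**Step 2: would such an artefact be declared significant?** With a standard two-proportion calculation (two-sided 5%, 80% power, patients treated as independent), the number per group needed to detect these changes runs from 270 (48% against 60%) to 2,036 (88% against 85%). The article gives no count of eligible patients. The assigned populations are 323,740 and 386,811, so groups of that order are plausible.

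**Step 3: dilution when s is equal.** A true 10-point gain among new-diagnosis patients appears as 10·(1 − s): 9.0, 7.5, 6.0 or 4.0 points at s = 0.10, 0.25, 0.40 or 0.60.

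**Step 4: masking.** On moderate/severe, q = 0.6 with s = 0.40 gives 0.40 + 0.60·0.6 = 0.76. If q truly rises to 0.7 while s falls to 0.20, the result is 0.20 + 0.80·0.7 = 0.76. A 10-point gain disappears.

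**Step 5: how coding alone could do this.** Take 100 mild recurrences, 50 of them given an antidepressant. If they are not recorded as new diagnoses, only the 50 treated patients enter and mild adequacy is 0% (clock at entry). If they are recorded as new diagnoses, all 100 enter and adequacy is 50%. For moderate/severe recurrences the same recoding moves the indicator from 100% to 50%. Prescribing is identical in both cases.

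**Step 6: after the fix.** With only new-diagnosis entrants, s = 0 and the indicator equals q. A 10-point gain reads as 10 points.

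**The case against.** The strongest reply is that a journal article condenses. Denominators and index dates for each indicator usually sit in a fuller plan, and Table 2 shows that the authors think that way: switch, augmentation and combination are proportions of new treatments, and the follow-up visits are counted from treatment start. The three indicators are also only 3 of 23 in Table 2 and none is named primary. Response, remission and the baseline evaluation indicators are not preset by a prescription. A baseline comparison of the areas is planned.

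Part of this stands. The treatment-anchored and baseline evaluation indicators need no change, and the matter is not critical to the study as a whole. But the article does state both the population and the adequacy definitions, and applied together as written they produce the problem, so this is more than an omitted detail. The baseline comparison could reveal an imbalance at the start but not a later shift in route mix.

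Three stronger readings are tempting, and the documents do not support them:

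- **A reader might infer that the indicators track route mix instead of care.** They track both: new-diagnosis entrants still respond, scaled by (1 − s), and the route mix is itself partly a result of care.
- **A reader might infer that every prescription-route patient fails the mild indicator.** That holds only with the clock at cohort entry. If it starts at the prior diagnosis, someone diagnosed more than eight weeks before the prescription can pass. That diagnosis could fall before the study or within the baseline period; the article does not say.
- **A reader might infer that INDI will lower the prescription-route share.** The article supports only that it can change it. Closer follow-up of previously diagnosed patients could raise it.

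**Conclusion.** The point holds as a flaw in stated rules, of moderate severity. Under the definitions as written, prescription-only entrants pass the moderate/severe indicator and, at entry, the anxiolytic-only indicator without conveying anything about the prescribing decision. They fail the mild indicator if the clock starts at entry. The dilution by (1 − s), and the bias when s differs between the groups compared, follow from the definitions. The size does not: the 3 to 12 points rest on assumed shares of 0.40 and 0.25 and an assumed q of 0.4 to 0.8, and the article gives no basis for estimating s. If s is small and similar everywhere, the consequence is slight dilution. Label: cheap improvement.

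**What to change.** Compute the three adequacy indicators only in patients who enter by a new diagnosis, with time counted from the diagnosis date. At minimum, report them separately by entry route, state the time origin of each, and base conclusions on the new-diagnosis group. In either case report the entry-route mix by arm and period. This matters even after the restriction, because a change in how recurrences are coded can still alter who counts as a new diagnosis. Leave the baseline evaluation indicators and the treatment-anchored indicators as they are defined.

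The change is to definition wording and uses the same records. The price is smaller denominators for three indicators, and no adequacy result for previously diagnosed patients in a new episode.
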